## Abstract

**Background:**

Cryptococcal meningitis (CM) is a leading cause of mortality among HIV-infected individuals in Africa. Poor outcomes from conventional antifungal therapies, unavailability of flucytosine, and difficulties administering 14 days of amphotericin B are key drivers of this mortality. Novel treatment regimes are needed. This study examines whether short-course high-dose liposomal amphotericin B (AmBisome), given with high dose fluconazole, is non-inferior (in terms of microbiological and clinical endpoints) to standard-dose 14-day courses of AmBisome plus high dose fluconazole for treatment of HIV-associated CM.

**Methodology/design:**

This is an adaptive open-label phase II/III randomised non-inferiority trial comparing alternative short course AmBisome regimens. Step 1 (phase II) will compare four treatment arms in 160 adult patients (≥18 years old) with a first episode of HIV-associated CM, using early fungicidal activity (EFA) as the primary outcome: 1) AmBisome 10 mg/kg day one (single dose); 2) AmBisome 10 mg/kg day one and AmBisome 5 mg/kg day three (two doses); 3) AmBisome 10 mg/kg day one, and AmBisome 5 mg/kg days three and seven (three doses); and 4) AmBisome 3 mg/kg/d for 14 days (control); all given with fluconazole 1200 mg daily for 14 days. STEP 2 (phase III) will enrol 300 participants and compare two treatment arms using all-cause mortality within 70 days as the primary outcome: 1) the shortest course AmBisome regimen found to be non-inferior in terms of EFA to the 14-day control arm in STEP 1, and 2) AmBisome 3 mg/kg/d for 14 days (control), both given with fluconazole 1200 mg daily for 14 days. STEP 2 analysis will include all patients from STEP 1 and STEP 2 taking the STEP 2 regimens. All patients will be followed for ten weeks, and mortality and safety data recorded. All patients will receive consolidation therapy with fluconazole 400–800 mg daily and ART in accordance with local guidelines. The primary analysis (for both STEP 1 and STEP 2) will be intention-to-treat.

**Trial registration:**

ISRCTN10248064. Date of Registration: 22 January 2014

## Background

Cryptococcal meningitis is a major cause of death in Sub-Saharan Africa, causing 10–20 % of all deaths in HIV infected cohorts, resulting in up to 500,000 deaths annually [1]. The poor outcomes reported using currently available antifungal therapy in African centres are a critical driver of this high mortality [2–6], and provide the impetus to develop novel treatment regimens for cryptococcal meningitis. Prior studies demonstrate the need for rapid initial clearance of cryptococcal infection for survival [2]. Conventional amphotericin B deoxycholate (AmB-d) induction for 2 weeks, given with oral flucytosine (5FC), is rapidly effective and still the gold standard [7–10], but safe delivery is not feasible or sustainable in most centres in Africa due to the need for 2 weeks hospitalisation and intravenous (iv) access, the cost of extra iv fluids and electrolytes, and above all, the availability and costs of rapid, reliable laboratory monitoring. Phlebitis with secondary infection [11], renal impairment, and anaemia are also significant problems with 14 days induction therapy with conventional AmB-d. Flucytosine is prohibitively expensive and not available in Africa [12, 13]. The alternative treatment, oral fluconazole, even at a dosage up to 1200 mg/d, as used currently in many centres in Africa, is still much less rapidly fungicidal than AmB-d, and mortality at 10 weeks remains in excess of 50 % [5, 14, 15].

In recent studies, using shorter-course conventional AmB-d (5–7 days) with high dose fluconazole [16, 17], no slowing of the rate of clearance of infection over the first 14 days was seen compared with 14 days of AmB-d, and there was a large gain in tolerability and therefore, ability to implement. The sustained effect of short-course AmB-d may be related to its prolonged mean residence time in brain tissue [18], and animal models suggest that abbreviated regimens of AmB-d (as short as 3 days) are as effective as full 14-day courses (Fig. 1) [18]. These data support the concept of short but still highly effective induction regimens.

**Fig. 1 Fig1:**
[figure not shown]
The effect of various regimens of amphotericin B for experimental cryptococcal meningoencephalitis. Amphotericin B deoxycholate 1 mg/kg was administered daily (**b**), every third day (**c**), as an abbreviated regimen for 3 consecutive days (**d**) and once (**e**). The solid arrows show the time of drug administration. The data in **a**-**e** represent the time course of infection in the cerebrospinal fluid (*CSF*). Each line represents the fungal burden in an individual rabbit. **f** shows the fungal density in the cerebrum at the end of the experiment. Each bar represents the mean fungal density ± standard error of the mean. There is no statistically significant difference in the cerebral fungal density of rabbits receiving daily therapy versus those receiving an abbreviated regimen of 1 mg/kg at 48, 72 and 96 h relative to inoculation: **p* = 1.00 (not significant), ***p* = 0.006, ****p* = <0.001, *****p* = <0.001, ******p* = 1.00 (not significant). *CFU*, colony-forming units. From Livermore J, Howard SJ, Sharp AD, et al. Efficacy of an abbreviated induction regimen of amphotericin B deoxycholate for cryptococcal meningoencephalitis: 3 days of therapy is equivalent to 14 days. MBio 2013; 5 (1): e00725-13. With permission

However, liposomal amphotericin B (AmBisome) would be even more suitable for this strategy than conventional AmB-d: it is less nephrotoxic, allowing much higher doses to be given safely, and also has excellent tissue penetration [19] and a long tissue half-life [20–23], raising the possibility of delivering highly effective induction therapy with very few (one to three) doses. Single doses of up to 15 mg/kg have been safely given to patients [22], and doses of 10 mg/kg are routinely given and have been shown to be efficacious for treatment of visceral leishmaniasis [24] and other invasive fungal infections [25].

Although AmBisome is recommended as a first-line agent for treating cryptococcal meningitis in several national guidelines [9, 26], there is uncertainty about the optimal dosing strategies [27]. Pharmacokinetic data from animal models [21] and humans [20] suggest that increasing AmBisome dose from the currently recommended 3–4 mg/kg may be required to facilitate safe, easy to administer, and effective intermittent dosing regimens and produce an antifungal effect that is as least as good as standard daily therapy [21]. High-dose fluconazole could be started with AmBisome, given evidence from randomised studies of an additive effect of high-dose fluconazole with conventional AmB-d [8, 28, 29], and to provide ongoing consolidation therapy.

Prior to any expanded access programme for AmBisome for cryptococcal infection, it is vital that we define the most clinically effective and most cost-effective schedules for its use. This study will provide the data needed. We propose to initially use early fungicidal activity (EFA), a highly efficient method to reliably test alternative treatment schedules in relatively small numbers of patients [2, 7, 14, 16, 17, 28, 30–34], to determine the fungicidal activity of several short-course dosing regimens. In addition to being a statistically powerful endpoint, EFA had been consistently shown to be independently associated with clinical outcome (Fig. 2) [2, 34]. After EFA evaluation in 160 patients, EFA, safety data and clinical efficacy data will be used to select the best performing intermittent dosing arm for ongoing clinical endpoint comparison with standard daily dosing. The principal aim of this study is to examine whether short-course high-dose AmBisome treatment, given with high-dose fluconazole, is non-inferior in terms of both microbiological and clinical endpoints to standard-dose 14-day courses of AmBisome plus high-dose fluconazole.

**Fig. 2 Fig2:**
[figure not shown]
Early fungicidal activity and mortality. The left hand panel shows the crude mortality rate (per person year) calculated over the first 2 weeks of treatment according to early fungicidal activity (EFA) in the 450 patients of the 501 anti-retroviral therapy (ART)-naive patients recruited in the studies listed in Reference 2 with slope (EFA) data. Patients have been stratified by EFA, with the slowest rate of clearance being 0–0.1 log_10_CFU/ml/day (equating to a 0 to 0.1 log drop in colony-forming units (*CFU*) per ml of cerebrospinal fluid (*CSF*) per day) and the highest rate of clearance being 0.5+ (equating to a half-log_10_ drop or more in CFU counts/ml of CSF per day). The right hand panel shows Kaplan Meier survival curves for the 501 ART-naive patients recruited into the studies listed in Reference 2 over the first 10 weeks of treatment, stratified by EFA. The slowest rates of clearance are indicated by the *solid black line* (EFA 0–0.1 decline in log_10_CFU/ml/day) and the most rapid rates of clearance are indicated by the small *dotted line* (EFA >0.3 decline in log_10_CFU/ml/day)

## Method/design

### Study design

This is an adaptive open label phase II/III randomised non-inferiority trial to compare alternative short course AmBisome regimens for the treatment of HIV-associated cryptococcal meningitis.

### Main hypothesis

Short-course high-dose AmBisome given with high dose fluconazole will be non-inferior to 2 weeks of daily dosed AmBisome-based induction therapy for the treatment of HIV-associated cryptococcal meningitis.

### Objectives

In step I (phase II), the primary objective is to determine the EFA of three alternative schedules of intermittent high-dose AmBisome in comparison with standard daily AmBisome, all given with fluconazole at 1,200 mg/d for the first 2 weeks, in induction therapy for HIV-associated cryptococcal meningitis. Secondary objectives are to determine the pharmacokinetic (PK) parameters and PK/pharmacodynamic (PD) associations of alternative schedules of intermittent high-dose AmBisome, to gather data on the clinical efficacy and safety of these alternative schedules of intermittent high-dose AmBisome in induction therapy for HIV-associated cryptococcal meningitis and to model the cost-effectiveness of these alternative schedules of intermittent high-dose AmBisome in induction therapy for HIV-associated cryptococcal meningitis. In step II (phase III), which includes transitioning to a phase III comparison of the shortest course AmBisome arm from step 1 meeting predefined minimum safety and efficacy standards with standard daily AmBisome dosing, the primary objective is to determine mortality within the first 10 weeks using short course high-dose AmBisome in comparison with standard daily AmBisome (for 14 days) for induction therapy of HIV-associated cryptococcal meningitis, both given with fluconazole at 1,200 mg/d for the first 2 weeks. Secondary objectives are to determine the EFA of alternative AmBisome schedules and culture status at 2 weeks, to examine the proportions of patients in each arm suffering clinical and laboratory-defined grade III/IV adverse events; median percentage change from baseline in laboratory-defined parameters by treatment arm and to determine health service costs by treatment arm.

### Setting

Step 1 will be carried out in Princess Marina Hospital (PMH), Gaborone, Botswana, which is a 500-bed tertiary care hospital in the capital city, and Bugando Medical Centre (with Sékou Touré Hospital and Butimba Hospital), Mwanza, Tanzania, which is the referral and teaching hospital for the Lake and Western zones of Tanzania, serving a population of 13 million. Step 2 will include the above plus Ifakara Health Institute, St Francis Referral Hospital, Ifakara, Tanzania, a 370-bed principal health care facility in the Kilombero district, Morogoro region, serving a catchment area of 400,000 people; Khayelitsha Hospital, with 150 adult beds, situated in the area with the highest HIV prevalence in the Western Cape, South Africa; and the Parirenyatwa General Hospital (Harare, Zimbabwe), which is one of the largest tertiary academic teaching hospitals in Zimbabwe and is affiliated with the University of Zimbabwe College of Health Sciences. A further southern African site is still to be confirmed.

### Outcome measures

In step 1 the primary outcome measure is EFA with alternative AmBisome schedules, and the secondary outcome measures include mortality at 2 and 10 weeks and time to death by treatment arm, unadjusted and adjusted for possible confounders and PK and PK/PD parameters. The PK-PD data will be modelled using population methodology, enabling a robust estimate of drug exposure in each patient, which can then be related to the observed pharmacodynamic data (e.g., the rate of decline in fungal density, or the time to undetectable cultures). Proportions of patients in each arm suffering clinical and laboratory-defined grade III/IV adverse events, and median percentage change from baseline in laboratory-defined parameters by treatment arm, and health service costs by treatment arm, will be determined. In step 2 the primary outcome measure will be mortality within 10 weeks by treatment arm. Secondary analysis will be performed with adjustment for possible confounders. EFA with alternative AmBisome schedules and culture status at 2 weeks, the proportion of patients in each arm suffering clinical and laboratory-defined grade III/IV adverse events, median percentage change from baseline in laboratory-defined parameters, and health service costs, will be evaluated by treatment arm as secondary outcome measures.

### Sample size

Step 1: using a non-inferiority design, assuming an EFA of 0.50 log colony forming units (CFU)/d, with standard deviation of 0.25 in the standard daily dosing control arm, an acceptable delta of 0.2, one-sided alpha of 0.025 and 90 % power, gives a sample size of 33 patients per arm. A total sample of 40 patients per arm (160 patients in total) will therefore be planned to allow for patients who die prior to having a second lumbar puncture (LP) to allow for an EFA measurement. An interim analysis will be done after 20 patients per arm to make adjustments, if necessary, to the required sample size, or to consider stopping one or more arms if any are found to result in significantly lower EFA than the control arm (*p* <0.05) and are deemed unlikely to meet the predefined non-inferiority criteria outlined above if continued to completion.

Step 2: a non-inferiority design has been chosen for assessment of the primary mortality endpoint, as a short course of AmBisome is not expected to be superior to the standard course, but is expected to have similar efficacy, while being easier to administer, affordable, and better tolerated. Using a non-inferiority design assuming 10-week mortality of 25 %, with an acceptable non-inferiority margin of 15 %, one-sided α = 0.025 and 90 % power, gives a sample size of 176 per arm. Using the 40 patients already recruited into each of the control arm and the short-course AmBisome arm from step 1 chosen for step 2, 136 additional patients per arm are required. To allow for withdrawals and losses to follow up a sample size of 150 patients per arm is planned, giving a total sample size for step 2 of 300 patients.

### Choice of non-inferiority margin

Step 1: previous studies demonstrate that the EFA of 14-day high-dose amphotericin-based regimens is in the region of 0.5 log CFU/d [31], and it is anticipated that standard-dose AmBisome regimens will be similar. The acceptable delta of 0.2 log CFU/d was selected on the basis of combined EFA data from over 500 patients included in prior studies (Fig. 2) suggesting that notable increases in mortality are not seen until the EFA drops below 0.3 log CFU/d.

Step 2: we anticipate that short-course AmBisome will have the same 10-week mortality as standard 14-day courses. A non-inferiority margin of 15 % below an assumed efficacy of 75 % (based upon recent data from South Africa and Botswana [3, 28, 35]) was considered acceptable based on the clinical acceptability and feasibility of the novel short-course regimens compared to standard 14-day courses of AmBisome, the current limited availability of conventional Amphotericin B-based treatments in much of Africa, reported treatment outcomes with Amphotericin B monotherapy [36] and high-dose fluconazole monotherapy in Africa [5, 14], and considerations relating to achievable recruitment rate projections. The Data Monitoring Committee (DMC) will regularly review mortality data, and appropriate increases to sample size will be made should the mortality in the control arm prove to be higher than anticipated.

### Inclusion and exclusion criteria

Patients to be included in the study are consecutive patients ≥18 years with a first episode of cryptococcal meningitis confirmed by either India ink or cryptococcal antigen test (CrAg) in the cerebrospinal fluid (CSF). They should be known to be HIV positive or willing to undertake an HIV test (which is positive) and agree to participate in the study. Pregnant (confirmed by urinary pregnancy test) or lactating patients, patients with a previous serious reaction to study drugs, or patients on antifungal treatment for more than 48 h or concomitant medication that is contraindicated with study drugs at the time of assessment for enrolment in the study, will be excluded. ART-naïve and experienced patients will be enrolled.

### Consent

Written informed consent to enter into the trial must be obtained from participants, or in the case of those with mental obtundation, from the patient’s guardian or a person with legal responsibility, after explanation of the aims, methods, benefits and potential hazards of the trial and before any trial-specific procedures are performed or any blood is taken for the trial. In the case of patients with altered mental status enrolled into the study, consent will be obtained as above as soon as the patient’s mental status improves, with care taken to ensure they understand that they are free to withdraw from the study and if they do so this will not jeopardise their immediate and future care. Participants who withdraw will revert to standard of care at the recruiting site (usually amphotericin B deoxycholate and fluconazole 800 mg daily for 2 weeks, or fluconazole 1,200 mg daily for 2 weeks). It will be made completely and unambiguously clear that the participant (or guardian) is free to refuse to participate in all or any aspect of the trial, at any time and for any reason, without incurring any penalty or affecting their treatment (or that of their guardian). Signed consent forms will be kept by the investigator and documented in the case report form (CRF) and a copy given to the participant or family.

### Allocation

Patients will be randomised individually using a computer-generated programme. Randomisation lists and sealed envelopes will be prepared by an independent statistician in advance and sent to the sites. Randomisation will be stratified by abnormal mental status and ART status on admission at each site to ensure equal numbers of severely ill patients and patients on ART in each group. An allocation ratio of 1:1 and block sizes of 8 will be used. The study monitor will audit the randomization and allocation concealment process to ensure there are no violations [37].

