### Interventions

In step 1, the four arms of the intervention are AmBisome 10 mg/kg on day 1 (single dose), AmBisome 10 mg/kg on day 1, AmBisome 5 mg/kg on day 3 (two doses), AmBisome 10 mg/kg on day 1, AmBisome 5 mg/kg on days 3 and 7 (three doses), and AmBisome 3 mg/kg/d for 14 days, which will act as the control (Fig. 3). In step 2 where the interest is in clinical endpoints, the intervention will be use of the shortest-course AmBisome regimen tested in step 1 (either regimen 1, 2 or 3 above) meeting the predefined safety and efficacy criteria and selected by the Trial Steering Committee (TSC) for further study, and AmBisome 3 mg/kg/d for 14 days used as the control. Note that all patients also receive fluconazole 1,200 mg/d for the first 2 weeks, followed by 800 mg/d until 10 weeks, and 200 mg/d thereafter. ART will be commenced 4 to 5 weeks after initiation of antifungal therapy. The trial clinical team is not blinded to treatment allocation, however, laboratory personnel performing CFU counts are blinded to treatment allocation.

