### Quality control and assurance

The study sponsor is St George’s University of London. The sites will be visited at regular intervals in order to monitor the conduct of the trial and ensure that the principles of International Conference of Harmonisation (ICH) good clinical practice (GCP) is being adhered to. These visits will be made by the trial manager/monitor from the sponsoring institution. The frequency of monitoring visits will be according to need but will be at least after recruitment of the first 10 to 15 patients at each site, and after recruitment of 50 % and 100 % of patients (trial closure). If issues arise the frequency of visits will be increased. Site initiation assessments will be conducted at each site prior to trial initiation. The trial manager will visit the sites and ensure that all training (including GCP and protocol-specific training) has been completed, that drug supply and equipment are in place and that all study staff are up to date on the protocol and procedures, and are competent to undertake the roles described for them in the standard operating procedures (SOPs). An external audit by the London School of Hygiene and Tropical Medicine will also be conducted towards the beginning of the trial. Central monitoring will be performed in addition to the on-site monitoring procedures. Cumulative monthly reports (including information on recruitment rates, withdrawals, losses to follow up) will be compiled by the trial manager/statistician and reviewed by the TMG. Bimonthly reports on grade III/IV adverse events (AEs)/serious adverse events (SAEs)/serious adverse reactions (SARs)/suspected unexpected serious adverse reaction (SUSARs) will be compiled by the trial manager/statistician and reviewed by the TMG.

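### As worded, the randomisation lists go to the open-label sites together with the sealed envelopes, and nothing in the article keeps them from enrolling staff

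*Protocol article*

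**What the plan says.** All of the following is in the protocol article.

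- **Allocation**, on what is shipped: "Randomisation lists and sealed envelopes will be prepared by an independent statistician in advance and sent to the sites".
- **Allocation**, on the scheme: "Randomisation will be stratified by abnormal mental status and ART status on admission at each site", and "An allocation ratio of 1:1 and block sizes of 8 will be used".
- **Allocation**, on the safeguard: "The study monitor will audit the randomization and allocation concealment process to ensure there are no violations".
- **Study design** calls the trial open label, and **Interventions** adds: "The trial clinical team is not blinded to treatment allocation, however, laboratory personnel performing CFU counts are blinded to treatment allocation".
- **Quality control and assurance** sets the minimum timing of monitoring visits: "at least after recruitment of the first 10 to 15 patients at each site, and after recruitment of 50 % and 100 % of patients".
- **Data collection and data management** bars site investigators from cumulative data by arm. That rule does not mention the randomisation list.

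**The concern.** A sealed envelope conceals an assignment only while the people who enrol patients cannot see the list from which it was filled. The sentence in Allocation puts both items at the site, and the clinical team there is unblinded by design. A recruiter who could read the list would know the next assignment in each stratum before deciding whether, when, or under which stratum to enrol a patient.

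At stake is the comparability of the arms on the step 2 primary endpoint, mortality within 10 weeks. Stratifying by mental status and ART status balances those two factors but not severity within a stratum. Under Sample size, the step 1 patients in the control arm and the selected arm count towards step 2 (40 of the required 176 per arm, or 40/176 = 23 %). Any selection in step 1 would therefore carry into the step 2 result.

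**Working it through.** The plan gives no figure on this point, so there is none to reproduce. The check is a reading of the text plus a small calculation of what a visible list would add.

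**1. Reading the sentence.** Lists and envelopes are the joint subject of both verbs, prepared and sent. Grammatically, both go to the sites. No other section says that the lists are sealed, held by someone outside recruitment, or kept centrally.

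**2. What the stated safeguard can do.** The monitor's audit takes place at visits guaranteed only at three recruitment milestones. It can find opened envelopes or assignments out of sequence. Reading a list leaves no such trace, so the audit cannot be relied on to prevent or detect it.

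**3. Predictability with envelopes only.** Inputs from Allocation and Interventions: blocks of 8, equal allocation, four arms in step 1 (2 per block) and two arms in step 2 (4 per block). Assume that staff know the block size and track every stratum. An assignment is certain when all places left in the block belong to one arm, so the expected number of certain assignments is the expected length of the run that ends the block.

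- Step 1: 1 + 1/7 = 8/7 = 1.14 of 8, which is 14 %.
- Step 2: 1 + 3/7 + (3×2)/(7×6) + (3×2×1)/(7×6×5) = 1 + 0.429 + 0.143 + 0.029 = 1.6 of 8, which is 20 %.

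A simulation of 100,000 blocks gave 14.3 % and 20.0 %. It also gave best-guess hit rates of 47 % in step 1 (chance 25 %) and 67 % in step 2 (chance 50 %).

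**4. Predictability if the list can be read.** Every assignment in every stratum is known, without counting. Varying the block size would reduce the figures in step 3 but would not change this one, so the two problems are separate.

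**5. Scale of a possible bias (assumed values, for illustration only).** Take the planned 25 % mortality in both arms. Suppose selection moves expected mortality by s points in one arm and by s points the other way in the other arm. The apparent difference is then 2s. For s from 0 to 3 points it ranges from 0 to 6 points in either direction: 22 % against 28 %, or 28 % against 22 %. The upper end is 6/15 = 40 % of the 15-point margin. No value of s can be taken from the article.

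**The case against.** The best defence is that this is one condensed sentence. Being sent to a site is not the same as being handed to recruiters. The list might go sealed to a pharmacist, and custody may be set out in the full protocol or the operating procedures, which are not shown. The same section specifies sealed envelopes, an independent statistician and an audit of concealment, all pointless if recruiters were meant to see the list. Quality control and assurance adds site initiation with training, central monitoring and an early external audit. Inclusion and exclusion criteria call for consecutive enrolment, so delaying or declining a patient because of the next assignment would depart from the protocol.

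Much of this stands. A reader might infer that enrolling staff will have the list, or that all assignments are in fact known in advance. The article says neither; full knowledge follows only if the list can be read. A reader might also infer that selection would flatter the short course, because staff would steer sicker patients to control. No section documents such wariness. Sample size describes the short course as expected to have similar efficacy and better tolerability, so any preference could run the other way or not exist.

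What does not stand is treating this as mere silence. The article does not simply omit who holds the lists; it states that they are sent to the sites. None of the oversight measures is said to cover custody of the list. Consecutive enrolment is also not self-enforcing: up to 48 hours of prior antifungal treatment is allowed, which leaves room to time an enrolment.

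**Conclusion.** The point holds as a defect in the stated procedure, not as evidence of compromised randomisation. As written, the lists reach the sites of an open-label trial, and nothing in the article keeps them from recruiters. If a recruiter can see a list, certain knowledge of assignments rises from at most about 14 % (step 1) or 20 % (step 2) to all of them.

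That contrast rests on two assumptions: the list is readable by enrolling staff, and, for the lower figures, staff know the block size and track every stratum. The effect on the mortality comparison could go either way and its size is unknown. The correction is worth making because concealment matters so much in this design and the remedy is nearly free. If only envelopes were ever meant to be sent, correcting the sentence settles the matter.

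**What to change.** Reword Allocation so that sites receive only sequentially numbered, opaque, sealed envelopes, and the lists stay with the independent statistician or another named party outside recruitment.

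The audit has to remain workable, because the monitor is the named auditor and withholding the lists without further provision would disable that check. Either the statistician releases to the monitor only the list entries for envelopes already opened, or the statistician does the reconciliation from the returned envelope records.

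The cost is a short change of wording, a change in what is shipped, and routing audit reconciliation through the statistician. Sample size, error rates and clinical procedures are unaffected. If lists have already been shipped, the sponsor should record who held them and whether they were sealed.

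### One fixed block size of 8, with site-held envelopes and an unblinded clinical team, would let staff who keep a tally deduce the end of each block; undisclosed varying sizes are a cheap, minor improvement.

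*Protocol article*

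**What the plan says.** Three features of the Allocation section matter here.

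- Block size: "An allocation ratio of 1:1 and block sizes of 8 will be used". No other size is named.
- Mechanism: "Randomisation lists and sealed envelopes will be prepared by an independent statistician in advance and sent to the sites".
- Strata: "Randomisation will be stratified by abnormal mental status and ART status on admission at each site".

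The Interventions section adds that "The trial clinical team is not blinded to treatment allocation, however, laboratory personnel performing CFU counts are blinded to treatment allocation".

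Two safeguards bear on enrolment. In the Allocation section, "The study monitor will audit the randomization and allocation concealment process to ensure there are no violations". The Inclusion and exclusion criteria call for consecutive patients.

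On scale, the abstract gives "Step 1 (phase II) will compare four treatment arms in 160 adult patients" and "STEP 2 (phase III) will enrol 300 participants and compare two treatment arms using all-cause mortality within 70 days as the primary outcome".

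**The concern.** A sealed envelope hides one assignment. It does not hide a sequence that can be worked out from the assignments already made. Within a permuted block of known length, the last allocation always follows from the others, and sometimes the one or more before it do too. Here the block length is single and published, the stratum of each patient is known on admission, and earlier allocations are visible because treatment is open. The sequence in each stratum also belongs to one site, so it can be followed locally.

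What is at stake is selection at enrolment. If the next arm is known, the timing of an approach or of consent could come to depend on it. Blinded CFU counting and an objective endpoint such as death protect outcome assessment, not the make-up of the arms. Stratifying by mental status covers only part of the variation in severity.

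**Working it through.** The article gives no figure for predictability, so there is none to reproduce. Its sample sizes (33 and 176 per arm) do reproduce from its stated inputs, and this point does not depend on them.

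**Inputs**
- Block size 8 and equal allocation (Allocation): 4+4 with two arms, 2+2+2+2 with four.
- Strata: mental status × ART status = 4 per site (Allocation).
- Sites (Setting): Step 1 has two, counting the Mwanza hospitals as one, so 2 × 4 = 8 strata. Step 2 has five named and one to be confirmed, so 5 × 4 = 20 to 6 × 4 = 24 strata.
- Patients: 160 in Step 1, 300 in Step 2 (abstract).

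An allocation counts as known when the earlier ones in the same block leave a single possibility. Let r be the number of allocations still to come in the block, including the next one.

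**Step 2, complete blocks.** The next allocation is known if all r remaining belong to one arm: P(r) = 2·C(4,r)/C(8,r).
- r = 1 (8th): 2·4/8 = 1
- r = 2 (7th): 2·6/28 = 42.9 %
- r = 3 (6th): 2·4/56 = 14.3 %
- r = 4 (5th): 2·1/70 = 2.9 %

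Sum = 1.6 of 8, or 20 %.

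**Step 1, complete blocks, exact arm.** P(r) = 4·C(2,r)/C(8,r).
- r = 1: 4·2/8 = 1
- r = 2: 4·1/28 = 14.3 %

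Sum = 1.14 of 8, or 14.3 %.

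**Step 1, complete blocks, control versus any short course.** Each block holds 2 control and 6 short-course places, so P(r) = [C(6,r) + C(2,r)]/C(8,r). For r = 1 to 6 this is 28/28, 16/28, 10/28, 6/28, 3/28 and 1/28. Sum = 64/28 = 2.29 of 8, or 28.6 %.

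**Incomplete blocks.** Step 2 averages 300/24 = 12.5 to 300/20 = 15 patients per stratum, so many blocks never fill and their predictable ends are never reached. Patients were simulated as falling at random into strata of equal size (an assumption):
- Step 2: about 48 of 300 (16 %) with 20 strata and about 45 of 300 (15 %) with 24.
- Step 1, 8 strata: about 19 of 160 exact arms (12 %) and about 40 of 160 control-versus-short-course assignments (25 %). If the Mwanza hospitals are counted separately, giving 16 strata, the figures are about 10 % and 22 %.

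**Best guess.** Always naming the arm with most places left succeeds 66.6 % of the time with two arms (chance 50 %) and 47 % with four (chance 25 %).

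**With randomly varying sizes.** The observer is assumed to know the set of sizes but not their order, which is generous to the observer if the scheme is withheld.
- Two arms, sizes 6/8/10: certain knowledge falls from 20 % to no more than about 3 %; best-guess success stays near 66 %.
- Four arms, sizes 4/8/12: exact-arm certainty falls from 14.3 % to about 3 %, and control-versus-short-course certainty from 28.6 % to about 7-8 %; best-guess success is about 45 %.

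**The case against.** The strongest reply is that the exposure is small, partly guarded, and not shown to do harm. Much of this stands.

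- The percentages are ceilings. Staff would have to know the block size and keep a running tally in each of four strata at their site. The 20 % also needs every block to fill.
- Patients are to be enrolled consecutively, which leaves little formal room to hold one back. The exclusion for more than 48 hours of antifungal treatment further limits waiting once treatment has begun.
- Under the Consent section, a patient who withdraws reverts to local standard care, usually without AmBisome. Steering a patient away from one arm could therefore cost that patient the study drug, which weakens the incentive.
- The monitor audits randomisation and concealment. That can reveal opened or misused envelopes. It cannot reveal that someone inferred the next arm from earlier ones, so here the reply falls short.
- This is a condensed article. The order of opening envelopes, registration before opening, and what sites are told may well be set out in the full protocol or the operating procedures. Their absence here is no fault. The single block size is different, because the article states it.

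A reader might infer that the mortality comparison will be biased. The document does not support that: it gives nothing from which the direction or size of any selection could be worked out. A reader might also infer that the lists themselves are open to recruiting staff, since lists and envelopes are both said to be sent to sites. The sentence does not say who at the site holds them, so this is a point to settle, not an established breach. Nor is the ratio of 1:1 an error for the four-arm step; it plainly means equal allocation.

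**Conclusion.** The point holds as a minor design weakness: the rule as stated makes part of the sequence deducible. The upper bound for Step 2 is 20 % of allocations with full blocks, or about 15-16 % (45-48 of 300) allowing for incomplete ones. For Step 1 it is about 12-14 % for the exact arm and about 25-29 % for control versus short course.

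These figures assume that staff know the block size and track allocations by stratum, that strata are of equal size, and that there are 8 strata in Step 1 and 20 to 24 in Step 2. They measure opportunity, not bias. The stated safeguards reduce the risk of selection without closing this route.

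**What to change.** Generate the lists with randomly varying block sizes, for example 4/8/12 with four arms and 6/8/10 with two. Do not disclose the sizes to sites. State that the lists stay away from recruiting staff, so that only sealed assignments reach them. Releasing each assignment only after the patient is registered would complete the concealment, if the full protocol does not already require it.

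This removes most of the certain knowledge. It does not stop educated guessing, so it should not be presented as making the sequence unpredictable. The cost is regenerating the lists and accepting slightly larger possible imbalance in small strata. Sample size is unchanged.
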